### Ethics Approval

Ethics approval to conduct the study was obtained from the Ethics Committee of the Medical Faculty of the Heinrich Heine University Duesseldorf (reference number: 2021-1364; April 6, 2021). The study was registered in the German Clinical Trials Register on April 21, 2021 (trial number: DRKS00024873). All study participants are fully informed about the study and are requested to provide informed consent.

### Sample Size Calculation

A number of 1000 steps were assumed as the minimal relevant effect. According to the previous study by De Cocker et al [14], the SD of the number of steps is ≤4500. This ensures a power of 80% for a 2-sided *t* test at the 5% level with a total of 638 patients (SAS, version 9.4, PROC POWER, TWOSAMPLEMEANS statement). A total of 798 participants were included in the study to compensate for an expected dropout rate of 25%. It should be considered that the power calculated here represents a lower limit because a noticeable gain in power is expected in the planned analysis owing to the adjustment for baseline characteristics of participants. Figure 2 shows the study design.

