**Methods:**

A controlled intervention trial examining the effects of an intervention addressing multiple levels (eg, individual level: website; organizational level: PA promotion in companies; community level: media campaigns and environmental changes) is being conducted. PA and various secondary outcomes will be assessed in 2 random samples of adults aged 25 to 75 years (n=399 in each city) at baseline and after 1 year.

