Furthermore, previous research suggests that combining individual-level step-count monitoring interventions with environmental approaches to promote PA at the community level, such as signage in parks and other green spaces and media campaigns, in complex intervention approaches leads to increased PA at the population level [14,15]. De Cocker et al [14] implemented a multistrategy community-based intervention aimed at promoting PA in adults aged ≥18 years, which was an adaptation of the “10,000 steps Rockhampton” (Queensland, Australia) program [16,17]. This complex intervention consisted of a website to track steps, a local media campaign, environmental modifications, and the sale and loan of pedometers. Intervention effects were examined in a controlled intervention trial comparing PA at baseline and after 1 year in 872 randomly selected participants (aged 25-75 years) from an entire city (Ghent, Belgium) to 810 living in a comparison city (Aalst, Belgium) [14]. In this study, an increase of 8% in the number of individuals reaching the recommended 10,000 steps was observed in the intervention city at the 1-year follow-up compared with no increase in the comparison city. The average number of daily steps walked increased by 896 (n=660; 95% CI 599-1192) in the intervention compared with no increase in the comparison city (n=634; mean change −135; 95% CI −432 to 162). Self-reported PA confirmed this result.

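### The dropout allowance is miscalculated: 798 participants cover a 20% loss, not the stated 25%, so even full recruitment would miss the required 638

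*Protocol article*

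**What the plan says.** All the relevant figures stand in the Methods of the protocol article, under Sample Size Calculation.

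- Effect: "A number of 1000 steps were assumed as the minimal relevant effect".
- Variability, attributed to the original Belgian trial: "the SD of the number of steps is ≤4500".
- Power: "This ensures a power of 80% for a 2-sided" t test, and the text continues "test at the 5% level with a total of 638 patients".
- Dropout: "A total of 798 participants were included in the study to compensate for an expected dropout rate of 25" percent.

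The Methods part of the abstract gives the same total by city, as "n=399 in each city" (2 × 399 = 798).

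The section closes by calling the calculated power a lower bound, because adjustment for participants' baseline characteristics is expected to add power. It gives no figure for that gain.

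**The concern.** A dropout rate is the share of enrolled participants who are lost. To finish with a required number N after a loss of d, one must enrol N/(1 − d). The 798 is instead what results from adding 25% to the required number, that is, N × (1 + d). The two formulas are close when d is small, but at 25% they differ by more than 50 participants.

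The article presents 798 as the number that offsets the expected loss. If it does not, the printed combination of sample size, dropout and power is wrong even for a trial that recruits in full. Readers of the results paper will judge the achieved sample against this statement.

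**Working it through.** **Inputs** (Sample Size Calculation; equal groups from the abstract): difference 1000 steps, SD 4500, two-sided alpha 5%, power 80%, 1:1 allocation, dropout 25%, total 798.

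**1. Reproduce the evaluable number.** The standardised difference is 1000/4500 = 0.2222. Solving the two-sample t test (noncentral t) for 80% power gives 318.84 per group, so 319 per group and 638 in total. This matches the article exactly; power at 319 per group is 80.0%.

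**2. Find where 798 comes from.**

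| Calculation | Result | Rounded up |
|---|---|---|
| 638 × (1 + 0.25) | 797.5 | 798 |
| 638/(1 − 0.25) | 850.7 | 851 |
| 638/(1 − 0.20) | 797.5 | 798 |

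Per city the pattern is the same: 319 × 1.25 = 398.75, so 399, whereas 319/0.75 = 425.3, so 426 (852 in total). The stated 798 therefore follows from multiplying by 1.25, or equivalently from dividing by 0.80. It does not follow from a 25% loss.

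**3. Loss that 798 can absorb.** 1 − 638/798 = 20.05%.

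**4. What 25% dropout leaves.** 798 × 0.75 = 598.5, about 299 per city. The shortfall against 638 is 39.5, about 40 participants. The shortfall in enrolment is 851 − 798 = 53, or 852 − 798 = 54 with equal groups; rounding cannot explain it.

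**5. Power at that number** (t test, difference 1000, SD 4500):

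| Evaluable total | Power |
|---|---|
| 638 | 80.0% |
| 598.5 | 77.5% |
| 598 | 77.4% |

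**6. Is a loss above 20% plausible?** The Introduction describes the original trial as "comparing PA at baseline and after 1 year in 872 randomly selected participants" in the intervention city and 810 in the comparison city, and it reports step changes for 660 and 634. Then 660/872 = 75.7% and 634/810 = 78.3%, or 24.3% and 21.7% fewer. Reading these as loss at 1 year is an inference: the article does not say why the numbers differ, and missing pedometer data could account for part of it. On that reading, both cities lost more than the 20% that 798 covers. Steps 1 to 5 do not depend on this.

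**The case against.** The strongest reply is that the consequence is small and the article has already hedged it. The section calls its power a lower limit because of baseline adjustment, and it gives 4500 as an upper bound for the SD. Either could make good the loss. With 598 evaluable participants, an SD of about 4,360 restores 80% (4500 × √(598/638) = 4357). So does a baseline-outcome correlation of about 0.26. The documents give no correlation; over an assumed range, adjusted power at 598 is 77.8% at 0.1, 81.2% at 0.3 and 87.9% at 0.5. Multiple imputation is also planned.

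This stands as a statement about size: the planned analysis may well have 80% power or more. It does not rescue the sentence. Both qualifications attach to the 80% computed at 638, and with 25% dropout 798 never delivers 638. The lower limit on the section's own assumptions is therefore about 77%. The correlation figures also take no account of the planned matching weights, which can reduce the effective sample size. Imputation does not turn 598 observed outcomes into 638, and the section itself treats dropout as something extra recruits must offset.

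One could also read the 25% as a mark-up on completers, but the text calls it a dropout rate.

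Finally, the Results section reports 626 enrolled as of March 2022, below 638 before any loss. That matters more for the achieved power, but it is a separate question and does not make the planning figure right.

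**Conclusion.** The concern holds. The three printed numbers, 638 evaluable, 25% dropout and 798 in total, cannot all be true. A total of 798 allows for 20% dropout; 25% would have required 851, or 852 with equal groups. At 25% dropout the design falls about 40 evaluable participants short and has 77.4% to 77.5% power instead of 80%.

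The power figures rest on the article's own assumptions: an unadjusted two-sided t test at 5%, a difference of 1000 steps, an SD at its stated maximum of 4500 and equal groups. They do not show that the planned adjusted and weighted analysis has less than 80% power, because the gain from adjustment and the cost of weighting are both unquantified. The error is certain and its effect on power is modest; no estimate or test is affected.

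**What to change.** Correct the dropout sentence in one of two ways.

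- Keep the 25% rate and state that a target of 798 would leave about 598 evaluable participants, with about 77% unadjusted power under the stated assumptions, and that 851 (852 with equal groups) would have been needed for 80%.
- Restate the allowance as 20%, which is what 798 covers.

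The first is preferable unless planning records show that 20% was the rate assumed, since changing the rate afterwards to fit the total would be a retrospective assumption. In either case, describe 798 as the planned number rather than the number included, since the Results section reports 626 enrolled. Use the corrected wording in the results paper and in the registry entry if the statement appears there.

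The cost is one sentence and a slightly less favourable figure. No additional enrolment and no change to the analysis is asked for.

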### Statistical Analyses

We will use the propensity score method for statistical analysis to allow for a nonrandomized design of the study. Specifically, the primary outcome will be estimated in a weighted 2-group comparison (intervention: yes vs no). For weighting, we will use matching weights [31] that are derived from a propensity score model for the intervention effect and an exhaustive list of covariates (Multimedia Appendix 2). The analysis will be blinded for the intervention effect and performed according to the intention-to-treat principle; missing values will be replaced via multiple imputation.

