## Results

Funding for this study was obtained in March 2020. Recruitment for this study and baseline data collection were conducted from May 2021 to March 2022 (as of March 2022, 626 participants were enrolled in the study). The intervention is being implemented in Duesseldorf for 1 year from April 2022 onward, and follow-up assessments will be conducted, starting in May 2023 (until September 2023). Data analysis will be performed in fall 2023, and the results will be published in spring 2024.

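### The sample size section reports 798 participants and treats 80% power as a floor, but 626 were enrolled at baseline close; on the plan's own t test with 25% dropout that gives about 67%

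*Protocol article*

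**What the plan says.** In the protocol article, Sample Size Calculation sets the target difference ("A number of 1000 steps were assumed as the minimal relevant effect") and takes the SD from the earlier Belgian trial ("the SD of the number of steps is ≤4500"). It concludes: "This ensures a power of 80% for a 2-sided *t* test at the 5% level with a total of 638 patients". The next sentence reports, in the past tense, that 798 people entered the study to allow for an expected 25% dropout. The section then says: "It should be considered that the power calculated here represents a lower limit because a noticeable gain in power is expected", giving adjustment for baseline characteristics in the planned analysis as the reason.

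The abstract's Methods paragraph gives the planned size as "2 random samples of adults aged 25 to 75 years (n=399 in each city"), that is 798 in total. The abstract's Results and the main Results section both report: "as of March 2022, 626 participants were enrolled in the study". Under Recruitment, invitations ran to the end of December 2021, baseline assessments were finished at the end of March 2022, and follow-up goes back to the same people. No top-up is described.

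Under Statistical Analyses, "the primary outcome will be estimated in a weighted 2-group comparison (intervention: yes vs no"), using matching weights from a propensity score model. Its covariates are listed in Multimedia Appendix 2, which is not shown.

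**The concern.** The 626 is in effect the final enrolment, because recruitment and baseline had closed and the intervention began in April 2022. A count of 798 reported as achieved cannot stand beside it. The 626 is also below the 638 evaluable participants that the calculation requires, before anyone drops out.

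The article gives one power statement for the primary outcome and does not revise it for 626. A reader who takes 80% as guaranteed could give a null result more weight against a 1000-step effect than the enrolled sample has been shown to support. Recruitment explains that a second sample was drawn so that the required numbers would be reached, and Strengths and Limitations mentions recruitment difficulty. Neither says that the target was missed.

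**Working it through.** **Inputs.** Difference 1000, SD 4500 (stated as an upper bound), two-sided 5%, 80% power, 638 evaluable and 25% dropout, all from Sample Size Calculation. Enrolled 626, from Results. The split of the 626 by city is not given, so I assume 1:1.

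**Formula.** Two-sample t test with N in total and equal groups: noncentrality = 1000 / (SD x sqrt(4/N)), with N - 2 degrees of freedom; power from the noncentral t distribution.

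**1. The plan's own figure.** N = 638: noncentrality 1000 / (4500 x sqrt(4/638)) = 2.807, power 80.0%. N = 636 gives 79.9%. The 638 reproduces.

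**2. Dropout inflation.** 638 x 1.25 = 797.5, rounded up to 798. To keep 638 after losing 25%, the number needed is 638 / 0.75 = 850.7, so 851. The 798 covers only 20% dropout (638 / 798 = 0.80). With 25% dropout, 798 x 0.75 = 598.5 completers, and power is 77.5%.

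**3. Power at the enrolled size.**

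| Case | Evaluable N | SD | Power |
|---|---|---|---|
| 626, no dropout | 626 | 4500 | 79.3% |
| 626, 20% dropout | 500.8 | 4500 | 69.9% |
| 626, 25% dropout | 469.5 | 4500 | 67.1% |
| 626, 25% dropout | 469.5 | 4250 | 72.0% |
| 626, 25% dropout | 469.5 | 4000 | 77.1% |

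A 45:55 split between the cities lowers the 67.1% only to 66.7%. At 469.5 completers and SD 4500, the difference detectable with 80% power is 1166 steps.

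**4. What adjustment must deliver.** Power of 80% at 469.5 completers needs an effective SD of about 3860. The reduction in variance is 1 - (3860/4500)^2 = 0.26, which corresponds to a correlation of about 0.51 between baseline and follow-up steps.

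**5. What the Belgian figures suggest.** The Introduction gives 95% CIs for mean change in Ghent (599 to 1192, n=660) and in the comparison city (-432 to 162, n=634). Treating these as simple intervals for a mean:
- Ghent: (1192 - 599) / 3.92 x sqrt(660) = 3886
- Comparison city: (162 + 432) / 3.92 x sqrt(634) = 3815

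A change-score analysis with SD about 3850 has 80.2% power at 469.5 completers (79.5% at 3886, 80.9% at 3815). If the SD is 4500 at both times, the implied correlation is 1 - 3850^2 / (2 x 4500^2) = 0.634. The residual SD with baseline steps as a covariate is then 4500 x sqrt(1 - 0.634^2) = 3480, and power is 87.4%. These adjusted figures allow for no loss of information from weighting.

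**The case against.** The strongest reply is that 67% is the power of a test the trial will not run. The planned analysis is a propensity-weighted comparison, and the lower-limit sentence refers to that analysis. This stands. A reader might infer that the planned analysis has only 67% power, and the documents do not support that: 4500 is an upper bound for the SD, and the Belgian intervals point to about 80-87% with adjustment for baseline steps.

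The sentence can also be read as comparing the t test with an adjusted analysis of the same 638 evaluable people. On that reading its reasoning is defensible, but it then says nothing about the enrolled sample, and the article offers no other power figure.

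A reader might also argue that matching weights discard information and push power far lower, to about 57-58% if they keep 80% of the sample's information. That retention figure has no source in the article, and the calculation gives no credit for balancing a prognostic baseline. If baseline steps are among the propensity covariates, weighting can itself recover precision. Multimedia Appendix 2 may list them; the Health Economic Evaluation section does so for its own matching. The absence of a baseline term from the article's short model description is therefore not an error.

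Finally, the 399 per city in the abstract is written as a plan and should not be read as a false report. The 626 is openly stated twice. What remains is the past-tense 798, the wrong inflation, and a power statement not updated for the sample obtained.

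**Conclusion.** The point holds as a mismatch between the stated and achieved size, together with an inflation error. At the enrolled size, 80% is not a floor: the plan's unadjusted t test has about 67% power at SD 4500 (72% at 4250, 77% at 4000), assuming a 1:1 split and the plan's own 25% dropout. The adjustment gain that the article presents as a bonus is needed to get back to 80%. It may well be enough, at about 80-87% if the Belgian change SD carries over, but the article does not quantify it or the loss from weighting. The documents therefore do not show that the planned analysis is underpowered. They show that its power at 626 is unstated and that the figure given does not apply to it.

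**What to change.** In Sample Size Calculation:

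- Describe 798 as the number planned and say that 626 were enrolled, with the split by city. Keep the target of 399 per city beside the achieved numbers, so that the design stays visible.
- Correct the inflation: 25% dropout needs 851, and 798 allows for 20%.
- Replace the lower-limit sentence with power at the enrolled size: about 67% unadjusted at SD 4500 with 25% dropout (detectable difference about 1170 steps), followed by the adjusted figure with its assumed baseline correlation and the effective sample size expected after weighting.

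Optionally, include baseline mean daily steps as a covariate in the weighted primary regression. They are already collected, and whether the propensity model already contains them cannot be seen from the article.

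The cost is a few sentences, one short calculation and, if the option is taken, one model term. No new participants or data are needed. The unadjusted power on record becomes less favourable.

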**Figure 2 figure2:**
[figure not shown]
Study design.

### Statistical Analyses

We will use the propensity score method for statistical analysis to allow for a nonrandomized design of the study. Specifically, the primary outcome will be estimated in a weighted 2-group comparison (intervention: yes vs no). For weighting, we will use matching weights [31] that are derived from a propensity score model for the intervention effect and an exhaustive list of covariates (Multimedia Appendix 2). The analysis will be blinded for the intervention effect and performed according to the intention-to-treat principle; missing values will be replaced via multiple imputation.

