Is the intervention “10,000 Steps Ghent” adaptable and transferrable to the context of city districts in the state of North Rhine-Westphalia?Is the intervention “10,000 Steps Duesseldorf” effective for the promotion of PA among residents of the districts involved?Do individuals located in the city that the intervention is implemented in (Duesseldorf) engage in more PA compared with individuals located in the control city (Wuppertal) after 1 year? Does the absolute number of steps taken per week increase more for individuals residing in the intervention city than in the control city?Does the proportion of those achieving the PA goal of 10,000 steps increase more in the intervention than in the control city after 1 year of potentially being able to participate in intervention activities?To what extent can these differences be attributed to the adoption, implementation, and maintenance of the intervention in the intervention city compared with the control city?What are the costs associated with the provision of the intervention? Does the intervention affect health care use and indirect costs? Is the intervention cost-effective in terms of additional costs per additional person who achieves the PA goal of 10,000 steps and additional costs per additional quality-adjusted life year (QALY) gained compared between the intervention and control cities after 1 year of potentially being able to participate in intervention activities?

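### The weighted two-group contrast fixed for the primary outcome does not secure the power gain that the sample size section expects from baseline adjustment

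*Protocol article*

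**What the plan says.** Under Methods, Sample Size Calculation, the protocol article sizes the trial on an unadjusted comparison. "A number of 1000 steps were assumed as the minimal relevant effect", "the SD of the number of steps is ≤4500", and 80% power is claimed for a two-sided *t* "test at the 5% level with a total of 638 patients". It then describes this power as a floor, because "a noticeable gain in power is expected in the planned analysis owing to the adjustment for baseline characteristics of participants".

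Under Methods, Statistical Analyses, the planned analysis is given: "Specifically, the primary outcome will be estimated in a weighted 2-group comparison (intervention: yes vs no". Matching weights come from a propensity score model whose covariates are listed in Multimedia Appendix 2, which is not shown. No covariate is named for the outcome model and no variance method is given. Missing values are to be multiply imputed.

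Two other places bear on this. The research questions at the end of the Introduction ask: "Does the absolute number of steps taken per week increase more for individuals residing in the intervention city than in the control city". The Health Economic Evaluation section names baseline steps among its own matching covariates; no such list is visible for the primary analysis.

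**The concern.** The sample size section makes a claim about the planned analysis, and the analysis section describes an analysis that may or may not meet it. Baseline steps are likely to be the strongest predictor of follow-up steps, and pedometer data are collected at both times on the same people. Yet as worded they can influence the primary result only through the weights.

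Weighting on an estimated propensity score is a form of baseline adjustment and can sharpen the estimate. Whether the reported interval shows this depends on whether baseline steps are in the propensity model and on how the variance is computed. The wording allows combinations in which the interval is too wide, the gain is absent, or the estimate is biased. At stake are the power and, in one case, the validity of the single primary comparison.

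**Working it through.** **1. The plan's own figure.** Difference 1000, SD 4500, two-sided 5%, 80% power. The exact noncentral *t* calculation gives 319 per group, 638 in total (power 0.8002). The stated 638 is reproduced with no baseline adjustment. The unadjusted standard error at 638 is 4500 × √(4/638) ≈ 356, a 95% half-width of 1.96 × 356 ≈ 698 steps.

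**2. The baseline–follow-up correlation (ρ).** It is not stated. The Introduction gives the Ghent study's changes with 95% CIs, so SD of change = (upper − lower)/(2 × 1.96) × √n:
- intervention city: (1192 − 599)/3.92 × √660 ≈ 3886
- comparison city: (162 + 432)/3.92 × √634 ≈ 3816

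With equal SDs at both times, ρ = 1 − SD(change)²/(2 × SD²). At SD 4500 this is 0.63–0.64, at SD 4000 0.53–0.55, and at SD 3500 0.38–0.41. Because 4500 is an upper bound, I use ρ = 0.4 and 0.63 as the range.

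**3. The gain available.** With baseline steps in the outcome model, the residual SD is 4500 × √(1 − ρ²): 4124 at ρ = 0.4 and 3495 at ρ = 0.63. Power at 638 becomes 86.5% and 95.1%. At ρ = 0.63 the half-width falls from 698 to 698 × 0.777 ≈ 542 steps.

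**4. What the weighted contrast delivers.** Simulation settings: N = 638, true effect 1000, SD 4500 throughout, normal data, five further covariates unrelated to outcome, 2000 runs per setting, no baseline imbalance. SD is the true sampling SD of the estimate; SE is the mean robust standard error with weights taken as fixed.

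| Analysis | ρ = 0.4 | ρ = 0.63 |
|---|---|---|
| Unadjusted | SD 351, power 80.0% | SD 349, power 80.1% |
| Weighted, baseline steps in propensity model, fixed-weight SE | SD 327, SE 357, coverage 96.5%, power 81.2% | SD 272, SE 357, coverage 98.9%, power 85.4% |
| Same estimator, SE equal to its true SD | power 85.5% | power 95.2% |
| Weighted, baseline steps not in propensity model | SD 365, SE 357, coverage 94.5%, power 77.7% | SD 359, SE 357, coverage 95.0%, power 80.8% |
| Weighted, baseline steps in both models | SD 327, SE 328, coverage 94.9%, power 85.5% | SD 272, SE 277, coverage 95.5%, power 95.0% |
| Weighted, baseline steps in outcome model only | SD 333, SE 328, coverage 94.5%, power 85.0% | SD 285, SE 277, coverage 94.1%, power 94.3% |

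Simulation error in power is about √(0.8 × 0.2/2000) ≈ 0.9 points. In the data behind the fourth row, the unadjusted contrast had power 77.9% and 81.2%, so weighting without baseline steps gained nothing. The third row uses the true SD as a stand-in for a variance that accounts for propensity estimation.

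- *Excess width* in the second row: 357/327 = 1.09 at ρ = 0.4 and 357/272 = 1.31 at ρ = 0.63. The approximation 1/√(1 − ρ²) gives 1.09 and 1.29.
- *Gain lost* in the second row: at ρ = 0.4, 85.5 − 81.2 = 4.3 of 5.5 available points; at ρ = 0.63, 95.2 − 85.4 = 9.8 of 15.1.

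**5. Bias if baseline steps are left out.** An imbalance of 0.2 SD (assumed, and not carried by the other covariates) shifts the estimate by ρ × 0.2 × 4500: 360 steps at ρ = 0.4 and 567 at ρ = 0.63. The simulated means were 1358 and 1560 for a true 1000. With baseline steps in the propensity model the means were 997 and 990; with them in the outcome model only, 995 and 996.

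**6. A second simulation** with 15 further covariates over the same range of ρ gave 79–85% power for the weighted contrast with a fixed-weight robust SE, against 85–94% once baseline steps were added to the outcome model.

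**The case against.** A reader might infer that the gain is lost and that the interval will be too wide. The documents do not support either as a fact. Multimedia Appendix 2 may well list baseline steps, and the variance method is a detail that a condensed article commonly leaves elsewhere, so its absence is not itself an error. With baseline steps in the propensity model, the weighted estimator is as precise as the regression-adjusted one (SD 272 for both at ρ = 0.63), and a bootstrap or stacked-sandwich variance would show it. The too-wide interval needs two conditions together: baseline steps in the propensity model and weights treated as known. Without the first, the interval is correctly sized for its estimator, and the problem is the missing gain and possible confounding.

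Nor does the sample size rest on the gain. The 638 comes from an unadjusted test, and the gain is an unquantified extra. The excess of about 30% belongs to the upper end of the correlation range.

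The compared variable might also be change from baseline, which would fit the research question. That would not secure the gain either. The SD of change is 4500 × √(2(1 − ρ)): 3871 at ρ = 0.63, above the 3495 from regression adjustment, and 4930 at ρ = 0.4, worse than no adjustment.

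What stands after all this is that the article fixes the form of the estimator and claims a gain for it, and the stated form does not guarantee the gain.

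**Conclusion.** The point holds conditionally. The expected gain is real and attainable, but the primary analysis as described secures it only if baseline steps are in the propensity model and the variance reflects that model's estimation. In the first of the other two cases the interval is about 5–10% too wide at correlation 0.4 and about 30% at 0.63, with most of the gain lost. In the second there is no gain, and baseline imbalance passes into the estimate.

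These sizes rest on a correlation inferred from the Ghent intervals and the SD bound, on simulated normal data, and on an assumed 0.2 SD imbalance for the bias. The stated 638 is unaffected.

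The gain matters in practice. The Abstract reports 626 enrolled by March 2022. After the plan's 25% dropout about 469 remain, with power of 67.3% unadjusted and 74.7% (ρ = 0.4) to 87.3% (ρ = 0.63) with baseline steps in the outcome model. That shortfall comes from enrolment, not from the choice of analysis.

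**What to change.** In Statistical Analyses, specify: *the primary outcome is follow-up mean daily steps, estimated in each imputed data set by matching-weighted linear regression on city with baseline mean daily steps as a covariate and robust standard errors*. This gives the gain with an ordinary robust standard error, and it adjusts directly for baseline steps whether or not they are in the propensity model.

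An alternative that is equivalent for precision is to keep the weighted contrast, state that baseline steps are in the propensity model, and use a bootstrap that re-estimates the weights or a stacked-sandwich variance. This takes more programming alongside multiple imputation.

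In Sample Size Calculation, attribute the expected gain to whichever adjustment is chosen.

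The cost is a sentence in each section before the analysis planned for fall 2023. No new data are needed, because baseline pedometer steps are already collected.
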